## Abstract

**Background:**

Depressive symptoms are common in patients with Parkinson’s disease and depression is a significant predictor of functional impairment, reduced quality of life and general well-being in Parkinson's disease. Despite the high prevalence of depression, evidence on the effectiveness and tolerability of antidepressants in this population is limited. The primary aim of this trial is to establish the clinical and cost effectiveness of escitalopram and nortriptyline for the treatment of depression in Parkinson’s disease.

**Methods:**

This is a multi-centre, double-blind, randomised placebo-controlled trial in 408 people with Parkinson’s disease with subsyndromal depression, major depressive disorder or persistent depressive disorder and a Beck Depression Inventory-II (BDI-II) score of 14 or above. Participants will be randomised into one of three groups, receiving either escitalopram, nortriptyline or placebo for 12 months. Trial participation is face-to-face, hybrid or remote. The primary outcome measure is the BDI-II score following 8 weeks of treatment. Secondary outcomes will be collected at baseline, 8, 26 and 52 weeks and following withdrawal, including severity of anxiety and depression scores as well as Parkinson’s disease motor severity, and ratings of non-motor symptoms, cognitive function, health-related quality of life, levodopa-equivalence dose, changes in medication, overall clinical effectiveness, capability, health and social care resource use, carer health-related quality of life, adverse effects and number of dropouts.

**Discussion:**

This trial aims to determine the effectiveness of escitalopram and nortriptyline for reducing depressive symptoms in Parkinson’s disease over 8 weeks, to provide information on the effect of these medications on anxiety and other non-motor symptoms in PD and on impact on patients and caregivers, and to examine their effect on change in motor severity.

**Trial registration:**

ClinicalTrials.gov Identifier: NCT03652870

Date of registration – 29^th^ August 2018

**Supplementary Information:**

The online version contains supplementary material available at 10.1186/s12883-022-02988-5.

## Background

Parkinson’s disease (PD) is a progressive neurological disorder that leads to increasing disability and functional decline. Approximately 35% of individuals with PD experience co-morbid depression or depressive symptoms throughout the course of their illness [1–3]. Depression is associated with functional impairment, cognitive decline, faster disease progression and reduced quality of life [4, 5]. Despite the high prevalence of depression, there is currently limited evidence on the efficacy of antidepressants for treating symptoms of depression in PD. The most common medications for treating depressive disorders in the UK are selective serotonin reuptake inhibitors (SSRIs), as recommended by the National Institute for Health and Care Excellence (NICE) guidelines [6]. However, SSRIs are often used cautiously in PD due to some preclinical studies and clinical reports of worsening parkinsonism [7, 8]. Additionally, other side effects such as fatigue or postural hypotension can occur and may already be pre-existing in PD [9, 10]. Furthermore, there have been reports about an increase in falls in patients on SSRIs, [11] and very rarely serotonin syndrome has been reported [12]. Tricyclic antidepressants (TCA), which have mixed properties including serotonin reuptake inhibition and noradrenaline reuptake inhibition, as well as anticholinergic and antihistamine actions, have similar efficacy to SSRIs [13, 14]. Their anticholinergic properties can also reduce both tremor and insomnia in PD. The TCA nortriptyline has also been suggested to have neuroprotective properties in pre-clinical studies by inhibition of aggregation and neurotoxicity of alpha-synuclein [15]. However, TCAs are currently recommended only as second line treatments for depression in PD due to increased risk of adverse side effects including, but not limited to, orthostatic hypotension, dry mouth, constipation, urinary retention, memory impairment, hallucinations and confusion. Some existing trial evidence supports the efficacy for both TCAs [13, 16, 17] and SSRIs [18] for depressive symptoms in PD but overall there is surprisingly little evidence available on the effectiveness of these antidepressants in PD, particularly in a real-life NHS setting in a representative population. Only two trials comparing SSRIs and TCAs have been reported, both with relatively small sample sizes of 15 to 18 per group respectively [16, 19], and of a treatment duration of 8 weeks and 30 days. Both SSRIs and TCAs, compared to placebo, reported improvement of depression, anxiety, dysphoria, vegetative symptoms and tolerability of the active agents. Whilst evidence suggests SSRIs are cost-effective compared with TCAs for major depression [14], no studies have explored this in depression in PD, and little information exists on the effect of antidepressant treatment in PD on health-related quality of life, carer burden and capability. No clinical trials have assessed the effect of nortriptyline on clinical disease progression in PD.

Due to the range of inconclusive and inconsistent evidence on both SSRIs and TCAs in the treatment of depression in PD, there is a need for conclusive trial evidence on both the clinical and cost-effectiveness of these two treatments to guide evidence-based treatment of depression in PD in the NHS in the short and longer term over 12 months, provide evidence on the effect on anxiety, cognition and other non-motor symptoms, health-related quality of life and carer burden, and to investigate potential effects on motor function over one year.

### Objectives

The primary objective of this trial is to establish the clinical and cost-effectiveness of escitalopram and of nortriptyline at 8 weeks compared to placebo in the treatment of depression in PD, in addition to standard psychological care in the NHS.

The secondary objectives are to establish i) whether after one year of treatment parkinsonism has deteriorated less in patients with Parkinson’s disease with depression on nortriptyline than on placebo; ii) the difference in adverse reactions between escitalopram and nortriptyline; iii) the long-term (after one year of treatment) clinical effectiveness and cost-effectiveness of escitalopram and nortriptyline compared to placebo; iv) the clinical effectiveness of escitalopram and of nortriptyline compared to placebo on anxiety, cognition, overall function, and health-related quality of life; and v) whether after one year of treatment parkinsonism has deteriorated more in patients with Parkinson’s disease with depression on escitalopram than on placebo.

## Methods/Design

### Study design

ADepT-PD is a multi-centre, double-blind, phase III randomised controlled trial with an internal pilot study and a parallel arm design (see Fig. 1). Participants will be randomly allocated 1:1:1 to receive escitalopram or nortriptyline or placebo.

**Fig. 1 Fig1:**
[figure not shown]
Trial diagram

### Participants and setting

Specialist PD clinicians will identify participants from approximately 30 sites across the United Kingdom, including neurology, care of the elderly, PD clinics, mental health trusts, primary care and community settings. The trial will be publicised through clinical networks, charities primary care surgeries and social media. Potential participants will be contacted for a pre-screening call and sent a participant information sheet detailing the trial. Suitability will be assessed by a trained clinician according to the eligibility criteria and fully informed consent will be retrieved from each participant.

Participants will be included if they: 1) have a diagnosis of idiopathic PD, including at least two of the three cardinal signs: rigidity, bradykinesia and rest tremor, 2) are aged 18 or above, 3) fulfil operationally defined subsyndromal depression (presence of two or more depressive symptoms, at least one of which has to include depressed mood or anhedonia, or diagnostic (*DSM-V*) criteria for a depressive disorder (i.e., major depressive disorder or persistent depressive disorder), 4) have a BDI-II score of 14 or above, 5) have optimised or stable antiparkinsonian medication for at least 4 weeks prior to randomisation with no plan to change up to primary endpoint (8 weeks) and 6) provide fully informed consent.

The study exclusion criteria are: 1) pregnancy, breastfeeding or childbearing potential without effective contraception, 2) inability to understand the participant information sheet or questionnaires, 3) a Montreal Cognitive Assessment (MoCA) score below 16 or lack of capacity to consent, 4) treatment with an antidepressant within 4 weeks of enrolment (except for a small dose of amitriptyline up to 30mg for indications other than depression), 5) severe liver failure, 6) contraindications to the study medication, including known QT-interval prolongation or congenital long QT syndrome, recent myocardial infarction (< 3 months), any degree of heart block or other cardiac arrhythmias precluding treatment with nortriptyline or escitalopram according to clinical judgement, 7) medications contraindicated on nortriptyline or escitalopram, including a). non-selective and selective irreversible monoamine oxidase (MAO) inhibitors within 14 days (the antiparkinsonian selective reversible MAO-B inhibitors rasagiline, selegiline and safinamide are not contraindicated) and b). Concomitant QT prolonging drugs, including domperidone, apomorphine at high doses (single dose or hourly rate of > 6mg), certain neuroleptics (not quetiapine or clozapine), quinine, class IA and III antiarrhythmics (amiodarone, dronedarone and disopryamide), the antihistamines astemizole, mizolastine, the antimicrobial agents sparfloxacin, moxifloxacin, erythromycin IV, pentamidine, anti-malarian treatment), and some antiretrovirals), 8) suicidal ideation or intent on the BDI-II item 9 and who, after clinical review of risk using the standardised Suicide Risk Management Protocol, need to be referred for immediate treatment, 9) participation in another trial of an investigational medicinal product or device within the last 30 days of randomization, and 10) any clinical condition which in the opinion/ clinical judgement of the investigator would make the patient unsuitable for the trial due to safety concerns.

### Randomisation and blinding

Following consent, participants will be randomly assigned to receive either escitalopram, nortriptyline or placebo. Randomisation will be completed using a minimisation algorithm by the randomisation service (Sealed Envelope Ltd., London). Randomisation will be done using a minimisation algorithm provided by the randomisation service (Sealed Envelope.com). The factors minimised on will include site, depression severity (BDI-II 14–19/20–63), Hoehn & Yahr disease severity staging in the ON medication stage (≤ 2.0/ ≥ 2.5), amitriptyline usage (yes/no)), clonazepam/benzodiazepine usage (yes/no), gabapentin/pregabalin usage (yes/no) and pramipexole/dopamine antagonist usage (yes/no).

The trial statistician will generate unique kit codes for every active/placebo trial medication bottle which will be entered into the web-based, password-protected, secure randomisation service provided by the independent data management company.

To maintain study blinding, all trial medication will be provided in bottles of identically appearing tablets. Site staff completing assessments will be kept blind to trial arm allocation, as will be the participants and the trial team and analysts.

### Assessment procedures

Participants will undergo assessment at baseline and 8, 26, 52 and following withdrawal at 56–60 weeks. All assessments will be performed by trained and suitably qualified members of the clinical trial team and completed either face-to-face or using a remote video conferencing software.

Assessments will include quantification of depressive and anxiety symptoms, PD motor features and non-motor symptoms, cognitive function, health-related quality of life, levodopa-equivalence dose, changes in medication, overall clinical effectiveness, capability, health and social care resource use, carer burden, adverse side effects and number of dropouts.

### Intervention

Participants will receive either:Escitalopram, target dose: 20mg if 65 years and under; or 10mg if > 65 years or in those with hepatic impairmentNortriptyline, target dose: 100mg if 65 years and under, or 50mg if > 65 years or in those with hepatic impairmentPlacebo

The initial dosage of trial medication will be as follows:5mg escitalopram increased by 5mg per day, at two-weekly intervals, to a maximum target of 20mg escitalopram per day25mg nortriptyline increased by 25mg per day, at two-weekly intervals, to a maximum target of 100mg nortriptyline per day

The dosing regime is shown in Tables 1 and 2. The dosage may decrease to the previous dose level if intolerable side effects occur.

**Table 1 Tab1:**
[figure not shown]
Dosing regime for participants aged 65 or under

**Table 2 Tab2:**
[figure not shown]
Dosing regime for participants aged over 65 or those with hepatic impairment

The medication will be sent to the participant’s home following randomisation. The total treatment duration will be 56 weeks.

Standard psychological care will be provided in conjunction, this may include referral to an Improving Access to Psychological Therapies service to receive Cognitive Behavioural Therapy or other forms of therapy.

After the primary endpoint at 8 weeks, all participants will continue on the same dose (*if applicable*) until the study visit at 52 weeks with an intermediate assessment at 26 weeks. If there is failure to respond to therapy and there is a clinical need to treat depression with an alternative agent, trial medication will be tapered and stopped and alternative therapy introduced as appropriate by their GP/clinician. If there is a need to stop the trial medication due to lack of efficacy or due to side effects, or the wish of the participant, participants will be encouraged to attend all study visits to obtain follow up assessments.

At the study assessment after 52 weeks on medication, the trial medication will be tapered off in dose reductions of 25mg for nortriptyline and 5mg for escitalopram every two weeks (8 weeks for participants 65 years or under and 4 weeks for participants > 65 years or those with hepatic impairment). Blinding of the participants and trial team will be maintained until the trial medication has been withdrawn but an unblinded member of the trial team will communicate the treatment allocation to the GP (and not the participant or the trial team) if they request unblinding earlier. For those who may wish to continue treatment at study end, liaison will be made with the GP to communicate the treatment allocation following unblinding by an unblinded member of the trial team.

### Adherence and retention

Participants will be required to record uptake and timing of trial medication using a dosing diary. A member of the research team will contact the participant at each time point as a reminder to complete the diary. A dosing diary discussion with the assessor will take place at baseline, weeks 8, 26 and 52.

If a participant chooses to discontinue their trial treatment, they will be encouraged to continue to be followed up as closely as possible to the follow-up schedule defined in the protocol. Participants who withdraw early from the trial will be asked to complete the BDI-II questionnaire to help evaluate their depressive symptoms at the time of withdrawal. Data already collected will be kept and included in analyses according to the intention to treat principle for all participants who stop follow up early.

### Primary outcome – Depressive symptoms

The primary outcome will be depressive symptoms after 8 weeks of treatment as measured using the Beck Depression Inventory-II (BDI-II), to assess effectiveness against placebo.

### Secondary outcomes

The following secondary outcomes will be measured at baseline, 8, 26 and 52 weeks of treatment and following withdrawal (Table 3 and supplementary table 1).

**Table 3 Tab3:** Outcome measures

**Domain**	**Measure(s)**	**Timepoint (week)**
Motor and non-motor PD symptoms	Movement Disorder Society Unified Parkinson’s Disease Rating Scale (MDS-UPDRS) during “On”	0, 8, 26, 52 and 56–60
	MDS-UPDRS part III during “Off” (optional)	0, 8, 26, 52 and 56–60
	Wearable sensor (optional)	0, 26 and 56–60
Depression	Beck Depression Inventory (BDI-II)	0, 26, 52 and 56–60
	Patient Health Questionnaire 9 (PHQ-9)	0, 8, 26 and 52
Anxiety	Parkinson Anxiety Scale (PAS)	0, 8, 26 and 52
Cognitive function	Montreal Cognitive Assessment (MoCA)	0, 8, 26, 52 and 56–60
Health-related Quality of life	EQ-5D-5L	0, 8, 26 and 52
Capability	ICECAP-O	0, 8, 26 and 52
Overall clinical effectiveness	Clinical Global Impression (CGI)	0, 8, 26 and 52
Health and social care resource use	Modified Client Service Receipt Inventory (CSRI) which incorporates the modified iVICQ	0, 8, 26 and 52
Levodopa-equivalence dose	Levodopa-equivalence dose	0, 8, 26 and 52
Changes in medication	Changes in concomitant medication	0, 8, 26, 52 and 56–60
Side effects	Modified Toronto Side Effects Scale and reporting of other adverse events	0, 8, 26 and 52
Carer-reported outcomes:		
Carer burden	EQ-5D-5L and Quality of Life questionnaire for carers (QOL carers) will be completed if the participant has a carer	0, 8, 26 and 52
Number of dropouts	Number of participants who dropout from the trial	8, 26 and 52

Following the 52 week assessment, the trial medication will be tapered off as above, and the participants will be assessed at 56–60 weeks on the BDI-II. MDS-UPDRS, MoCA concomitant mediation and reporting of Adverse Events.

### Sample size

A total of 408 participants will be recruited in the full trial. The primary outcome is change in depressive symptoms measured using the BDI-II after 8 weeks of trial treatment. For 90% power and a significance level of 0.025 (for each comparison to preserve studywise alpha), 113 participants are needed per group to detect a 3-point BDI-II difference [SD for change 6.35] [20, 21] for the escitalopram–placebo and the nortriptyline–placebo comparisons at 8 weeks. Allowing for 20% attrition, 136 participants will be required per randomised group (408 overall).

With this sample size, the study will have 90% power (1-beta) to find a mean difference of change of 3 points on the Movement Disorders Society Unified Parkinson’s Disease Rating Scale (MDS-UPDRS) motor subscale (part 3), with a nominal alpha of 0.025 for each active comparison, taking the effective SD from [22].

For the estimation of adverse reactions we will use the Modified Toronto Side Effects Scale which elicits rates of side effects. We will use estimation and provide 95% confidence intervals around the difference in percentage side effects for each item, however the width of these confidence intervals will depend upon their position on the binomial distribution. Thus, a trial with 136 subjects in each experimental condition will provide 95% confidence intervals on the comparison between active agents ± 12% when the rate of events is around 50%, and ± 7% when the rate of events is around 10%.

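### 408 randomised participants do not yield 113 evaluable per group at the stated 20% attrition; 136 × 0.8 is 108.8

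*Protocol article*

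**What the plan says.** The protocol article, under Sample size, sets the calculation up with "For 90% power and a significance level of 0.025", applied to each active–placebo comparison, and an "SD for change 6.35". From these it concludes that "113 participants are needed per group to detect a 3-point BDI-II difference". The next step is the one at issue: "Allowing for 20% attrition, 136 participants will be required per randomised group (408 overall".

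The total is stated again at the start of the same section ("A total of 408 participants will be recruited in the full trial") and in the Methods part of the abstract ("double-blind, randomised placebo-controlled trial in 408 people"). Allocation is 1:1:1 (Study design), so 408 means 136 in each group. The article prints no formula for the attrition step, and nothing in it defines attrition as anything other than a share of those randomised.

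**The concern.** The randomised number is meant to leave the required number evaluable once the expected loss has occurred. Here it does not: 20% off 136 is below 113. The likely cause is a common slip, in which the evaluable number is multiplied by one plus the attrition rate instead of being divided by one minus it.

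At stake is the statement on which the trial's size rests. If attrition is as the protocol assumes, neither primary comparison has the number or the power that the Sample size section claims for it. Any reader can check this from the printed figures.

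**Working it through.** **Inputs**, all from the protocol article:
- difference δ = 3 BDI-II points, SD of change σ = 6.35, power 90%, α = 0.025 per comparison, attrition 20%, 136 per group and 408 overall (Sample size)
- equal allocation (Study design)

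The article does not say whether α is one- or two-sided. Two-sided is assumed because it reproduces the stated 113.

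**Step 1: reproduce the evaluable number.** Normal approximation, two-sided:

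n = 2 (σ/δ)² (z₀.₉₈₇₅ + z₀.₉₀)² = 2 × (6.35/3)² × (2.2414 + 1.2816)² = 111.2, so 112.

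With the t-test (noncentral t), power is 89.9% at n = 112 and 90.1% at n = 113. So 113 is the smallest group size that reaches 90%, which matches the protocol. A one-sided α of 0.025 gives 95 by the normal approximation and does not fit.

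**Step 2: reproduce the randomised number.**
- 113 × (1 + 0.20) = 135.6, rounded up to 136; 3 × 136 = 408. This is the protocol's figure.
- 113 / (1 − 0.20) = 141.25, rounded up to 142; 3 × 142 = 426.

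Rounding cannot bridge the gap. Dividing by 0.8 gives 140 even from a starting value of 112.

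**Step 3: what 136 per group delivers at 20% attrition.** 136 × 0.80 = 108.8 evaluable, against 113 required. This holds however 136 was obtained.

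**Step 4: power and detectable difference** (two-sided t-test, δ = 3, σ = 6.35, α = 0.025):

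| Evaluable per group | Power |
|---|---|
| 108 | 88.7% |
| 108.8 | 88.9% |
| 109 | 89.0% |
| 113 | 90.1% |

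The normal approximation gives 89.1% at 108 and 89.4% at 109, so the conclusion does not depend on the method. At 108.8 per group, the difference detectable with 90% power is 3.05 points by the t-test (3.03 by the normal approximation).

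**Step 5: attrition that 408 can absorb.** 1 − 113/136 = 0.169. Up to 16.9% loss leaves 113 per group.

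**Step 6: size of the gap.** 142 − 136 = 6 per group; 426 − 408 = 18 overall; 18/426 = 4%.

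**The case against.** The strongest reply concerns power. The Statistical analysis section says that the primary comparison of change is made conditional on the baseline score, whereas the 113 and the 88.9% both come from an unadjusted comparison of change. Adjustment multiplies the variance by 1 − r², where r is the correlation between change and baseline. The article does not give r, so what follows is an assumption shown over a range. If 6.35 is a raw SD of change and the baseline and week-8 variances are equal, then r² = (1 − ρ)/2, with ρ the correlation between baseline and week 8. At 108.8 per group, power would be about 96% for ρ = 0.5, 93.5% for 0.7, 92% for 0.8, 90.5% for 0.9 and 89.7% for 0.95. The planned analysis may therefore well reach 90% in practice. That much stands. But the article does not use this argument to justify 136, the origin of 6.35 cannot be checked here, and no adjustment turns 108.8 evaluable participants into 113.

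Other points also have some weight:
- **Retention.** Participants who stop treatment are encouraged to stay in follow-up, and early withdrawers are asked for a BDI-II (Adherence and retention). Loss may come in below 20%. That would make 136 sufficient, but it would not make the 20% statement correct, and a score at withdrawal is not a week-8 score.
- **The route to 136.** Multiplication by 1.2 is an inference. It fits the printed figure exactly and is the only standard route that does, but the finding does not rest on it.
- **Size.** A loss of about one percentage point of power would not change the design or the interpretation of the trial. This is accepted.

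**Conclusion.** The point holds. The Sample size section is wrong as written: at its own 20% attrition, 408 randomised gives about 109 evaluable per group, not 113, and the number consistent with its inputs is 142 per group (426 overall).

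The consequence is a slight shortfall, not a materially underpowered trial. On the stated calculation, power is about 89% instead of 90% for each of the two primary comparisons. These power figures rest on a two-sided α of 0.025, an unadjusted comparison and an SD of change of 6.35. The shortfall in numbers needs none of these assumptions, only the printed 113, 136 and 20%. It needs correcting because the trial's size and power claim contradicts its own inputs and the correction is almost free.

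**What to change.** Keep 408 and correct the attrition sentence in the Sample size section. Suggested content: with 136 randomised per group (408 overall), 113 per group remain evaluable, with 90% power, at up to about 17% attrition; at 20% attrition about 109 per group remain, with about 89% power for a 3-point difference. Any other trial document that repeats the sample-size statement should carry the same wording.

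This costs one sentence and a stated power about one point lower. It needs no further participants and no change to design or analysis. If the sponsor prefers to rely on baseline adjustment to support 90% power at 20% attrition, the assumed correlation and its source should be stated.

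The alternative is to keep both 20% attrition and 90% power. The target then becomes 142 per group and 426 overall, in the Sample size section and in the abstract, at the cost of recruiting 18 more participants.

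### The side-effect precision of ±12% and ±7% is stated for all 136 randomised per arm; with the plan's own 20% attrition it is about ±13% and ±8%

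*Protocol article*

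**What the plan says.** All the figures are in the protocol article, Sample size. For the primary outcome, at 90% power and a two-sided level of 0.025 per comparison, "113 participants are needed per group to detect a 3-point BDI-II difference [SD for change 6.35"]. The next step is "Allowing for 20% attrition, 136 participants will be required per randomised group (408 overall"). This is the only attrition allowance in the article, and it belongs to the 8-week BDI-II calculation.

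For side effects, the plan is to "provide 95% confidence intervals around the difference in percentage side effects for each item" of the Modified Toronto Side Effects Scale. The expected width is given by the statement that "a trial with 136 subjects in each experimental condition will provide 95% confidence intervals on the comparison between active agents" of ± "12% when the rate of events is around 50%, and ± 7% when the rate of events is around 10"%. Table 3 collects the scale at weeks 0, 8, 26 and 52. Objective (ii) is the difference in adverse reactions between escitalopram and nortriptyline.

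Between these two statements the section says of MDS-UPDRS part III: "With this sample size, the study will have 90% power (1-beta) to find a mean difference of change of 3 points". The level is 0.025 per active comparison and the SD is taken from a cited source without its value. No time point is named. Objectives (i) and (v), on the course of parkinsonism, are set after one year of treatment.

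**The concern.** The same section uses two different numbers per arm. For the BDI-II it accepts that about a fifth of those randomised will give no outcome. For side effects it takes the randomised number as if everyone will be assessed. The Toronto scale is completed at visits, so a participant lost before week 8 has a baseline record only and cannot enter a comparison of side effects on treatment.

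Objective (ii) has no hypothesis test and no power statement. The expected interval width is all that supports the claim that the trial is large enough for it, so that width should be the one the plan expects to deliver.

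**Working it through.** **Inputs** (Sample size section): 136 randomised and 113 evaluable per arm, 20% attrition, 95% confidence, event rates of 50% and 10%.

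**Step 1: the expected evaluable number.** 113 × 1.2 = 135.6, rounded up to 136. So 136 was reached by adding 20% to 113, not by dividing by 0.8 (113 / 0.8 = 141.25). A true 20% loss from 136 leaves 136 × 0.8 = 108.8, about 109. The plan's own evaluable figure is 113. The range 109 to 113 covers both.

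**Step 2: reproduce the stated precision.** The half-width for a difference of two proportions with common rate p and n per arm is 1.96 × √(2p(1 − p)/n). At n = 136:

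- p = 0.5: 1.96 × √(0.5/136) = 11.88%
- p = 0.1: 1.96 × √(0.18/136) = 7.13%

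These round to the stated 12% and 7%, so the stated figures rest on all 136.

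**Step 3: repeat at the expected evaluable number.**

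| n per arm | rate 50% | rate 10% | width relative to n = 136 |
|---|---|---|---|
| 136 | 11.9% | 7.1% | 1.00 |
| 113 | 13.0% | 7.8% | √(136/113) = 1.10 |
| 109 | 13.3% | 8.0% | √(136/109) = 1.12 |

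The choice of interval does not alter this. Newcombe, Agresti–Caffo and score intervals give 11.7 to 11.8% and 7.3 to 7.5% at 136. At 109 to 113 they give 12.8 to 13.2% and 7.9 to 8.3%.

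**Step 4: the motor power, conditional only.** The SD value is not given, so the 90% cannot be reproduced. It can only be turned round. With the normal approximation and two-sided level 0.025, the SD that gives 90% power for 3 points is 3 / [(2.241 + 1.282) × √(2/n)].

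- If 90% was computed on 113 evaluable, the implied SD is 6.40 and power at 109 is 88.9%.
- If 90% was computed on all 136, the implied SD is 7.02, and power is 83.4% at 113 and 81.9% at 109.

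The article does not say which base was used. It gives no retention figure for week 52.

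**The case against.** The precision sentence is conditional on 136 per arm and is arithmetically correct on that condition. The figures are indicative: the rates are approximate and the text says the width varies with the rate. The sample size was set by the BDI-II, no decision threshold rests on the side-effect intervals, and the achieved intervals will be reported in any case. All of that stands, and it keeps the point small. It does not remove the mismatch, because the section itself does not expect 136 per arm to be assessed.

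A reader might infer that anyone lost to follow-up contributes nothing. That is too broad. A participant lost after week 8 has already given a week-8 score. The Adherence and retention section keeps data already collected and encourages those who stop treatment to stay in follow-up. The argument needs only the loss before week 8, and that is the time point to which the 20% allowance is attached.

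A reader might also infer that the MDS-UPDRS power is overstated, because its objectives are at one year and no further attrition is allowed for. The document does not establish that. The claim comes directly after the step from 113 to 136, so the allowance may already be included, and then power at 109 is about 89% against the stated 90%. The lower figure of about 82% requires assuming that the calculation used all 136 with no loss. Loss by week 52 beyond 20% is plausible, but the article does not state it. The SD value is a detail that an article may leave to the full protocol.

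**Conclusion.** The side-effect precision is stated too favourably on the plan's own attrition: about ±13% and ±8%, not ±12% and ±7%. The intervals are 10 to 12% wider than stated, about one percentage point. This assumes that the planned loss occurs before the first on-treatment Toronto score at week 8, as the allowance implies, and that the two arms lose similar numbers. The outcome is secondary and for estimation only, and neither the sample size nor the primary analysis is affected. The correction is worth making because the expected width is the only size justification for objective (ii).

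The motor power is a secondary and unproven point. The text leaves open which time point and which number per arm the 90% refers to. That calls for a check and does not show an error.

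**What to change.** In Sample size, restate the expected 95% confidence half-widths for the comparison of the two active arms as about ±13% at a 50% rate and ±8% at a 10% rate, and say that they refer to 109 to 113 evaluable participants per arm. For MDS-UPDRS part III, check that the 90% holds for the number expected to be evaluable at week 52, and restate the power if it does not.

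The cost is a wording change in the protocol or the statistical analysis plan and a slightly less favourable precision figure. No extra participants and no new data are needed.
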